##### Sensitivity Analyses

Testing for carryover effects will not be carried out as the risks of carryover were minimized in the design by allowing for a wash-out period to allow most patients admitted in the first period to complete their hospitalization before the hospital crosses over and by only considering index hospitalizations.

Sensitivity analyses for primary and secondary outcomes will exclude patients who are extremely unlikely to receive the study fluids (direct hospital admissions to psychiatry), those who are otherwise healthy (patients who have vaginal and cesarean births and elective surgical admissions <24 hours), and those who may have been exposed to both types of study fluids (lengths of stay spanning both FLUID study periods).

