##### Secondary Outcomes

The secondary outcomes are 90-day death, hospital readmission within 90 days of the index hospitalization, and requirement for new dialysis within 90 days; and for surgical patients, requirement for reoperation, postoperative reintubation in the postoperative assessment unit, ED visits within 90 days, hospital length of stay, and discharge to facility other than home. All secondary outcomes will be obtained at the patient level from DAD and National Ambulatory Care Reporting System.

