**Secondary outcomes, n (%)**					
	Death within 90 days of index admission				
	Readmission to the hospital within 90 days of index admission				
	New dialysis within 90 days of index admission				
	Requirement for postoperative intubation in the postoperative assessment unit				
	Requirement for reoperation within 90 days of index admission				
	ED^a^ visit within 90 days within 90 days of index admission				
	Hospital length of stay, median (IQR)				
	Discharge to a facility other than home				

^a^ED: emergency department.

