##### Subgroup Analyses

The primary outcome will be analyzed within the following subgroups of patients who are at a higher risk for exposure to fluids and with greater risk profiles and or severity of illness than other patients. These include age (<18, 18 to ≤65, 66 to ≤80, and >80 years); sex; type of hospital admission (medical, surgical, pregnancy and childbirth, mental health); elective and urgent or emergent surgical admissions, surgical admissions <24 hours, surgical subgroups (as described in Table 3); admission to ICU, infection alone and infection and organ dysfunction, infection alone and infection and organ dysfunction and ICU admission, trauma with injury severity score (ISS) ≥12, trauma with ISS=12 and ICU admission, traumatic brain injury, traumatic brain injury and ICU admission, and comorbidity index (Elixhauser) [43]. These subgroup analyses will be implemented without covariate adjustment and using the cluster-level summary method as described for the primary and secondary outcomes but applied to subgroup differences within each cluster. Results will be presented using forest plots.

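### Two sensitivity exclusions depend on length of stay yet are also applied to length of stay as an outcome: a minor, cheaply repaired flaw that leaves the primary analysis untouched

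*Protocol article*

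**What the plan says.** The protocol article's Sensitivity Analyses section opens with "Sensitivity analyses for primary and secondary outcomes will exclude patients" and lists three kinds of patient. One kind is unlikely to be exposed: "patients who are extremely unlikely to receive the study fluids (direct hospital admissions to psychiatry". A second is low risk: "those who are otherwise healthy (patients who have vaginal and cesarean births and elective surgical admissions <24 hours". A third may have had both fluids: "those who may have been exposed to both types of study fluids (lengths of stay spanning both FLUID study periods". The psychiatry and birth exclusions do not depend on how long the patient stayed. The other two do.

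The Secondary Outcomes section includes "hospital length of stay, and discharge to facility other than home", and Table 4 has a row "Hospital length of stay, median (IQR" with columns for a difference, its interval and a P value. Under Analytical Framework every outcome is tested for superiority. The Subgroup Analyses section uses a similar cut, "surgical admissions <24 hours", as a subgroup for the primary outcome. Analysis Populations keeps all admitted patients in the primary analysis.

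**The concern.** Length of stay is known only at discharge, after the allocated fluid has been in use. An exclusion based on it can therefore remove different kinds of patient from the two fluids if the fluid affects discharge time, and the trial tests whether it does.

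This has two consequences. When length of stay is the outcome, removing stays under 24 hours in elective surgery cuts away the part of the distribution into which a faster discharge would move patients, so the estimate shrinks. For the primary outcome, a fluid that speeds discharge would lose more low-risk patients to the exclusion, and those left would look slightly sicker even with no effect on death or readmission. A gap between the sensitivity and main results could then partly reflect selection. The short-stay surgical subgroup raises the same issue, because its membership would be settled after allocation.

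**Working it through.** The point disputes no figure in the plan, so the check is one of size.

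**Inputs from the article.** Stay: median 2 days, 10th and 90th percentiles 1 and 5.2 days (Discussion). Run-out of 14 days, then one week to switch (Trial Design). 1500 patients per hospital per month (Sample Size), so 1500 × 3 = 4500 per hospital and period. Length of stay is analysed on the log scale (Primary Analyses).

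**Assumed.** Lognormal stay; elective-surgery median 1.2-2.0 days; median 2.0-2.5 days for other patients; elective share f of 10%-30%; one fluid shortens every stay by 5%, a log shift of ln 0.95 = -0.0513. Covariate adjustment and the other exclusions are ignored.

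**1. Log SD.** ln(5.2/2)/1.2816 = 0.746.

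**2. Within elective surgery.** With a = -μ/σ, the share under one day is P = Φ(a), and the mean log stay of those kept is m = μ + σφ(a)/(1 - Φ(a)).

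| Elective median | Share under 24 h, before and after shift | Difference in m | Fraction of true effect |
|---|---|---|---|
| 1.2 days | 40.3%, 43.0% | -0.0211 | 41% |
| 1.5 days | 29.3%, 31.7% | -0.0251 | 49% |
| 2.0 days | 17.6%, 19.5% | -0.0307 | 60% |

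**3. Across all patients, as planned.** Only elective stays are cut, so the mean is M = [f(1 - P)m + (1 - f)μ_other] / [f(1 - P) + (1 - f)].

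Example with f = 20%, elective median 1.2 and other median 2.5 days:
- Before: (0.1193 × 0.6665 + 0.80 × 0.9163)/0.9193 = 0.8839.
- After: (0.1139 × 0.6454 + 0.80 × 0.8650)/0.9139 = 0.8376.
- Difference -0.0463; -0.0463/-0.0513 = 90% retained.

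Over the grid, retention is 95%-98% at a 10% share, 90%-95% at 20% and 85%-92% at 30%. A true ratio of 0.95 would be estimated at about 0.951 to 0.957.

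**4. Sensitivity to the log SD.** The value 0.746 comes from the upper tail. The median and 10th percentile give ln 2/1.2816 = 0.541. Retention within elective surgery at median 2.0 is then 70% instead of 60%. The least favourable all-patient cell (30% share, medians 1.2 and 2.5) goes from 85% to (0.7873 - 0.8286)/-0.0513 = 81%. The message does not change.

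**5. Primary outcome, no true effect.** Assume a 90-day risk of 4% in patients who cross the 24-hour line and 10% in other elective patients. The artefact within elective surgery is (P_after - P_before)/(1 - P_after) × (0.10 - 0.04) = 0.28, 0.21 and 0.14 points for medians 1.2, 1.5 and 2.0. Multiplied by a 20% share this is about 0.06, 0.04 and 0.03 points.

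A wider grid allows for the change in case mix: share 10%-30%, 10%-30% of these under 24 hours, a shift of 1-5 points, and risks of 5% in short stays, 8% in shifted patients and 16% overall. It gives 0.01 to 0.15 points. Its largest cell is (0.16 - 0.0045 - 0.0012)/0.895 - (0.16 - 0.0045)/0.91 = 0.0015.

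**6. Spanning stays.** Even the last period 1 admission must stay more than 14 days to reach the switch week and more than 21 days to reach the period 2 window. Averaging the fitted tail (median 2, log SD 0.746) over 84 admission days gives about 1.0 and 0.23 patients per 4500. Real tails are probably heavier, so this is a lower guide.

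**The case against.** The strongest reply is that the 24-hour category may be fixed at admission. Table 3 lists it as a type of surgical admission among baseline characteristics, and Table 1 puts that item at enrollment. This leaves the meaning open but does not settle it: Table 3 also lists ICU admission as a baseline item, and no section says that the limit refers to planned stay. The need to clarify stands.

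A reader might infer from the 41%-60% row that the length-of-stay sensitivity analysis loses about half the effect. The article does not support that, because no length-of-stay analysis within elective surgery alone is planned and subgroups cover only the primary outcome. One caution: the sentence in Secondary Outcomes could be read as limiting length of stay to surgical patients. The Abstract and Table 4 show no such limit, and the working follows them. Under the narrower reading the elective share, and hence the loss, would be larger.

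A reader might also object that the spanning rule removes only period 1 patients while equally long period 2 stays remain. That is true, but half the sites have each fluid in period 1, and the planned regression of within-cluster differences on clusters minus 2 degrees of freedom implies a term for sequence or period. A removal confined to period 1 therefore cancels to first order. Only a fluid effect on very long stays would remain, in very few patients.

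**Conclusion.** The point holds as a minor one. As written, and with the limit read as observed stay, two exclusions condition on a post-allocation variable that the trial tests, and the length-of-stay sensitivity analysis truncates its own outcome. Bias arises only if the fluid changes length of stay. Under the stated assumptions about 85%-98% of a 5% effect is retained, and the primary-outcome artefact is about 0.03-0.06 points at a 20% elective share. The elective share, elective median, risks and 5% effect are assumptions, not figures from the article.

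It would go too far to conclude that the sensitivity analyses cannot test the robustness of the primary result: an artefact of this size is small against 1 point, and the primary analysis keeps every admitted patient. No size was worked out for the short-stay surgical subgroup, so there the point is one of principle only.

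**What to change.** Do not apply the 24-hour and spanning exclusions when length of stay is the outcome.

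For the other outcomes, and for the short-stay surgical subgroup, define short-stay surgery by facts fixed at admission: planned day-case status, or a list of procedures whose median stay was under 24 hours in pre-trial administrative data. If planned stay was already meant, say so.

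The spanning exclusion may stay for the other outcomes if it is reported as conditioning on post-allocation stay. Dropping the last enrolment weeks would not replace it, since an earlier admission with a long enough stay could still meet both fluids. Excluding all elective surgery would depart from the stated aim of removing otherwise healthy patients. The birth and psychiatry exclusions need no change.

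The cost is a change of wording and perhaps one procedure list, made before the data set is received. Some listed-procedure patients who stay longer would also be excluded, a small loss of precision in sensitivity analyses only.

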##### Cost-Effectiveness Analyses

We will conduct a cost-effectiveness analysis of RL and NS from the perspective of the Canadian public health care payer using a hybrid decision tree and Markov models. A decision tree with a 90-day time horizon will be used to determine the effects of each fluid on mortality, requirement for dialysis, and health system costs. Baseline characteristics will be based on the concurrent trial. Surviving patients will enter a Markov component of the model [44] in which outcomes and costs will be modeled in annual cycles for the remainder of the patient’s lifespan. Based on close consultations with coinvestigators, the model structure will incorporate the long-term consequences of fluid therapy; potential health stats may include dialysis-free, dialysis, and death. In each Markov cycle patients could remain in their existing health state, progress to the more severe state, or die. Transition probabilities between health states will be obtained from the concurrent trial and utility values will be derived from the published literature. Direct health care costs, such as physician costs and dialysis costs, will be derived from provincial health administrative data available at ICES and from publicly available sources in Canada.

The model outcomes will include incremental cost per one death averted and incremental cost per one QALY gained. An annual discount rate of 1.5% will be applied to both costs and health outcomes, as recommended by Canada’s economic evaluation guideline [45]. Scenario analyses will be conducted to assess the impact of structural uncertainty and the uncertainty associated with model assumptions on cost-effectiveness results. The model will be fully probabilistic and address parameter uncertainty.

##### Missing Data

The prevalence of missing data is expected to be minimal as outcomes will be obtained from ICES. Nevertheless, missing data for each outcome will be summarized by the treatment group. If substantial missingness is observed (>10%), sensitivity to missing data will be examined under a range of missing-not-at-random scenarios by assuming first that all patients with missing outcomes had the event of interest and then that all patients with missing outcomes did not have the event of interest.

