### Sample Size

A total of 16 hospital sites (including the 4 pilot sites) will yield data on approximately 144,000 hospital admissions. It required 12 sites in a 2-period cluster crossover trial over 6 months to achieve 80% power with a 2-sided α of 0.05 to detect a minimum clinically important absolute difference of 1% in the primary outcome in favor of RL, assuming a proportion of 0.16 in the NS condition, a within-period intracluster correlation coefficient of 0.006, a cluster autocorrelation coefficient of 0.95, and an average of 1500 patients per hospital per month [37]. These estimates were calculated from available routinely collected data for January 1 to December 31, 2013, for all eligible hospitals across the province of Ontario, Canada. Our calculations account for nonadherence based on pilot data (94% adherence NS, 80% RL). We added 2 clusters as an approximate small sample correction [38] and a further 2 to account for cluster size variation [38], for a final sample size of 16 sites.

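### The missing-outcome scenarios give both fluids the same value, so they do not bound the effect when missingness is balanced, and the 10% trigger is large against a 1-point target

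*Protocol article*

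**What the plan says.** The Missing Data section of the protocol article expects few missing outcomes, because they come from provincial administrative data. It will describe missingness for each outcome by fluid group, whatever its level. A sensitivity analysis follows only under a condition, "If substantial missingness is observed (>10" (the figure is a percentage). The section speaks of a range of missing-not-at-random scenarios but defines two: "assuming first that all patients with missing outcomes had the event of interest", and then the reverse, that no patient with a missing outcome had it. Neither scenario distinguishes the fluids.

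The Sample Size section sets the effect of interest as a "minimum clinically important absolute difference of 1% in the primary outcome in favor of RL", "assuming a proportion of 0.16 in the NS condition". The Participant Follow-Up section expects almost complete follow-up and names one source of loss, the few patients who leave Ontario within 90 days.

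**The concern.** A missing-not-at-random analysis of a treatment comparison should show how far the effect could move if missing patients fared differently under the two fluids. Assigning one value to everyone does not do this. When the fluids have the same missing fraction, the two scenarios are one calculation, and it returns a slightly smaller version of the observed difference. Balanced missingness is also the likely case here, since every hospital contributes to both fluids and all outcomes come from one data holder.

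The second issue is scale. The trial is built around a difference of 1 percentage point, while the check begins only above 10% missing. If missingness were a few percent, the plan would have no prespecified sensitivity analysis. If it exceeded 10% and were balanced, the two agreeing results could be read as reassurance that they do not provide.

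**Working it through.** **Inputs.** From Sample Size: 16% under NS, a 1-point reduction (so 15% under RL), "a within-period intracluster correlation coefficient of 0.006", cluster autocorrelation 0.95, 1500 patients per hospital per month, "2-sided α of 0.05". From the analysis methods: t-distribution with clusters minus 2 degrees of freedom. From Missing Data: the 10% trigger and the two scenarios. The missing fractions and the risk gaps among the missing are my assumptions; the article gives none.

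**The plan's own figure.** The article states: "It required 12 sites in a 2-period cluster crossover trial over 6 months to achieve 80% power". Take each 12-week period as 3 months, so 4500 patients per cluster-period, and average the two binomial variances: (0.16 × 0.84 + 0.15 × 0.85)/2 = 0.13095. The variance of one cluster's difference is 2 × 0.13095 × [0.994/4500 + 0.006 × 0.05] = 0.0001364. The number of clusters is (1.96 + 0.842)² × 0.0001364/0.01² = 10.7, so 11, or 12 as the next even number. The total is 16 × 6 × 1500 = 144,000, as stated. This reads the 1 point as the intention-to-treat difference. The missing-data formulas below do not depend on the sample-size calculation.

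**Formula.** With missing fractions m_RL and m_NS, and event risks f_RL and f_NS assigned to the missing:

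difference = [(1 − m_RL) × 15% + m_RL × f_RL] − [(1 − m_NS) × 16% + m_NS × f_NS]

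**Balanced missingness.** If m_RL = m_NS = m and f_RL = f_NS, the assigned terms cancel and (1 − m) × (−1.00) remains, whether f is 0 or 1. The same holds within each hospital, so the two scenarios also agree after equal-weight averaging of unadjusted differences. In percentage points (RL minus NS):

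| Missing in each arm | Both planned scenarios | RL all event, NS none | RL none, NS all event |
|---|---|---|---|
| 0.5% | −0.995 | −0.495 | −1.495 |
| 1% | −0.99 | +0.01 | −1.99 |
| 5% | −0.95 | +4.05 | −5.95 |
| 10% | −0.90 | +9.10 | −10.90 |
| 15% | −0.85 | +14.15 | −15.85 |

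The last two columns are (1 − m) × (−1.00) ± 100m points. The plan does not compute them.

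**Unbalanced missingness.** Here the planned scenarios do move:

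- 10% NS, 11% RL, all event: (0.89 × 15 + 11) − (0.90 × 16 + 10) = 24.35 − 24.40 = −0.05. All non-event: 13.35 − 14.40 = −1.05.
- 8% NS, 12% RL, all event: 25.20 − 22.72 = +2.48. All non-event: 13.20 − 14.72 = −1.52.

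**Tipping points with balanced missingness.** Let the missing under RL have an event risk higher by D than the missing under NS. The difference is zero when (1 − m) × 0.01 = m × D, so m = 0.01/(0.01 + D):

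| Gap D among the missing | Missing fraction at which the estimate reaches zero |
|---|---|
| 100 points (opposite extremes) | 0.99% |
| 20 points | 4.8% |
| 10 points | 9.1% |
| 5 points | 16.7% |

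**Significance.** With 16 sites the standard error is √(0.0001364/16) = 0.29 point. With 14 degrees of freedom the confidence half-width is 0.63 point. Holding the standard error fixed, an observed 1-point difference loses significance at m = (0.01 − 0.00626)/(D + 0.01): about 0.4% missing for opposite extremes, 1.8% for a 20-point gap and 3.4% for a 10-point gap. These figures ignore covariate adjustment and variation in cluster size.

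**The case against.** The strongest reply is that this is a contingency clause unlikely to be used. Loss is expected to be very small, its one named source is leaving the province, and nothing in the article suggests that the outcomes of those patients would differ sharply by stocked fluid. Missingness is also tabulated by fluid at any level, so a reader could work out a crude bound from the published counts. All of this stands, and it keeps the practical weight low.

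Two stronger readings are tempting and do not hold. A reader might infer that the planned analysis cannot test robustness at all, because the sign can never change. That is true only when missingness is balanced, which the plan does not assume. At 8% against 12% missing, the all-event scenario reverses the sign.

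A reader might also infer that the trigger comes ten times too late, from 0.99% against 10%. That ratio needs every missing RL patient to have the event and no missing NS patient to have it, a 100-point gap against an assumed control risk of 16%. With a 10-point gap the estimate reaches zero close to the trigger, and with a 5-point gap above it. Significance could go earlier, so a lower threshold is arguable, but no particular factor is established.

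**Conclusion.** The point holds in a limited form. The planned scenarios detect a difference between fluids in the amount of missing data. They do not examine a difference in outcome among the missing, and under balanced missingness they give one shrunken estimate and no bound. The 10% trigger is given no justification and is large for a 1-point target: the point estimate could reach zero at about 1% missing under opposite extremes, and at about 5% to 9% under an assumed gap of 20 to 10 points. These figures assume an observed difference equal to the design target, equal missing fractions and no covariate adjustment. It is a worthwhile refinement rather than a threat to the trial's conclusions, provided that follow-up is as complete as expected.

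**What to change.** Remove the 10% condition. At whatever level of missingness is observed, run an arm-specific tipping-point analysis: vary the assumed event risk among missing patients separately under RL and NS, re-estimate the effect with the same cluster-level method at each combination, and report where the estimate reaches zero and where the confidence interval first includes zero. The two opposite extremes are the end points. The two scenarios now planned are the remaining corners of the same grid, so nothing is lost. A replacement threshold such as 0.5% or 1% would be a matter of preference, and none is needed.

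The cost is a change of wording and a few more runs. The extreme bounds will look wide if missingness is not tiny, so the grid between them should carry the interpretation. By the article's own account the plan was written before the trial data were received, so a change made before then would not be informed by results.

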##### Statistical Software

The statistical analyses will be performed with SAS (version 9.4; SAS Institute) and R (R Foundation for Statistical Computing).

#### Dissemination of Findings

Guided by a theory and evidence-informed dissemination planning guide [46], the plan will be guided by the dissemination objective, knowledge of user audiences, dissemination strategies targeted to the audience, and the expertise required to deliver the strategies and required resources. Knowledge user audiences will certainly include health policy leads, health system managers, clinicians, patients and caregivers, and researchers. Depending on the magnitude, strength, and nature of the findings, the dissemination goals could range from increasing awareness of the findings by interested parties to influencing hospital policy and physician prescribing practices at the provincial, national, and international levels. To reach researchers and clinicians, we plan rapid open access publication of our study results in a high-impact journal. We will hold webinars to present and discuss our study results with hospital administrators and clinicians in Ontario. We will reach out to local and provincial social media and traditional media to inform the public, patients, and caregivers about our study findings. If RL is found to be superior to NS, then we will have a particular dissemination focus on health policy and decision-makers to encourage the switch to use these fluids in Ontario hospitals. Finally, we will communicate and present our study findings to the Council of Academic Hospitals of Ontario and plan to host meetings targeted toward health policy decision-makers and high-level hospital administrators (chief executive officers) around the province of Ontario.

